### Data Analysis

Descriptive analysis of index cases visiting health centers will be baselined to further assess differences in yield by groups. Chi-square test and Student *t* test for categorical and continuous variables will be used to assess differences in baseline characteristics among groups. Regression analysis and adjusting for confounding variables will be used to evaluate the primary outcome and relative risk, and its 95% CIs will be calculated. Significance will be set at .05. The multiple imputation method will be used to generate possible values for missing values. This is considered the gold standard for dealing with missing values. Data will be analyzed in Stata v12 (StataCorp LLC).

The methodology of analysis of the social and sexual networks will be used from an egocentric perspective. Structural measures of the network will be calculated, such as the size of the network, number of direct links, density, the geodesic average distance, diameter of ego’s network, and measures of centrality, such as the degree of intermediation of a contact or index case. Furthermore, we will compare social network, density, and structure. Network measurements will be done using the R statistical package.

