**Methods:**

This is a multicenter randomized controlled trial with a proportional stratification of the sample by center and random allocation of participants to the 3 arms of the study (simple Web-based intervention, game Web-based intervention, and control). This study is being conducted by midwives, gynecologists, and physicians in the sexual and reproductive areas of the primary health care centers.

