## Methods

### Design

This is an unblinded 3-armed randomized controlled trial, assigning patients to each arm of the study through the proportionally stratified sample of patients by health center, which will test the primary hypothesis that a greater proportion of partners will be informed about their exposure to STIs (syphilis, chlamydia, or gonococcus) in the intervention groups compared with the control group. We will randomize 416 young and recently diagnosed index cases in 1 of the 7 centers of the study. The researcher responsible for analyzing the data will be blind to group allocation.

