### Sample Size

Young population accessing all centers of study within a year is around 400. They have been randomly distributed in 3 arms, according to the Bonferroni correction, to allow multiple comparisons of outcomes with a significance level of *P*=.016. The trial is expected to have 10% of withdrawals after recruitment within the intervention groups and 20% of withdrawals after recruitment within the control group. Therefore, to have at least 120 participants in each 1 of the groups, 133 are recruited in each 1 of the intervention groups and 150 are recruited in the control group. The random list ratio is 1:1:1.28. To achieve this sample, participant recruitment is allowed for a period ranging from 13 to 18 months.

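### Baseline significance tests between three randomised arms, followed by adjustment for unnamed confounders, are a poor basis for the primary model, which should be fixed in advance and include centre

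*Protocol article*

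**What the plan says.** The Data Analysis section states that chi-square and Student t tests "for categorical and continuous variables will be used to assess differences in baseline characteristics among groups". The next sentence gives the primary analysis: "Regression analysis and adjusting for confounding variables will be used to evaluate the primary outcome and relative risk". No covariate is named, no rule for choosing covariates is given, and centre is not mentioned. The same section adds "Significance will be set at .05", while the Sample Size section works at .016.

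On the design side, the abstract describes "proportional stratification of the sample by center and random allocation of participants to the 3 arms". The Design section speaks of "assigning patients to each arm of the study through the proportionally stratified sample of patients by health center". The section on randomisation and consent assigns the sample to 7 centres in proportion to their activity. Table 1 gives targets by centre and arm, with centre totals from 34 to 82. The Data Collection section shows that the recruiting centre is recorded on the index-case questionnaire and that the health professional registers the diagnosed STI.

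**The concern.** Under sound randomisation, any baseline difference between arms arose by chance. A p-value for that difference therefore tests a hypothesis already known to be true, and it says nothing about whether the variable matters for the outcome. Confounding is the vocabulary of observational studies. In a randomised trial, a covariate earns its place because it was used in the design or is expected to predict the outcome, and it is chosen before the data are seen.

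With the two sentences side by side, an analyst could reasonably let imbalances found at baseline decide the adjustment. The primary relative risk would then depend on which chance differences appeared, and more than one answer would be consistent with the plan. The one factor the design does use, centre, also has no stated place in the model. If centre predicts notification, some precision is given up without need. The Results section reports recruitment well behind schedule, so that precision is worth keeping.

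**Working it through.** **The plan's own figures.** The point itself rests on no stated figure. The recruitment targets reproduce to within one: 120/(1 − 0.10) = 133.3 per intervention arm (133 stated), 120/(1 − 0.20) = 150 in control, and 133 + 133 + 150 = 416. The 120 per arm cannot be checked, because the article gives no effect size, control rate or power.

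**Spurious baseline differences.** The index-case questionnaire yields about 10 to 12 testable items: centre, age, sex, country of birth, mother's country of birth, education, sex of partners, number of partners, two web-use items, diagnosed STI, and intention to notify. With no true imbalance and k independent tests at .05 (independence is an assumption), P(at least one significant) = 1 − 0.95^k:
- k = 10: 1 − 0.95^10 = 0.401
- k = 11: 0.431
- k = 12: 0.460

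The expected number of false positives is 0.05k, that is 0.5 to 0.6.

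**Student t test with three arms.** The test has to be run pairwise, three times per continuous variable. A normal simulation with arms of 150, 133 and 133 and a two-sided .05 cut-off (400,000 draws) gave at least one significant pair in 12.2% of draws.

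**Leaving centre out.** Assumptions: arms are balanced within centres, centre explains a share R² of outcome variance, and the effect would give 80% power with no centre effect. A normal approximation is used, with c the two-sided critical value and θ = c + 0.842 (at .05, θ = 1.960 + 0.842 = 2.802).
- True size with centre omitted: 2[1 − Φ(c/√(1 − R²))]
- Power with centre omitted: Φ((θ − c)/√(1 − R²))
- Power with centre included: Φ(θ/√(1 − R²) − c)

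Example at .05 with R² = 10%: √0.9 = 0.949. Omitted, Φ(0.842/0.949) = 81.3%. Included, Φ(2.802/0.949 − 1.960) = 84.0%.

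| R² (assumed) | True size at nominal .05 / .016 | Power at .05, omitted v included | Power at .016, omitted v included |
|---|---|---|---|
| 2% | .048 / .015 | 80.2% v 80.8% | 80.2% v 80.9% |
| 5% | .044 / .0135 | 80.6% v 82.0% | 80.6% v 82.3% |
| 10% | .039 / .011 | 81.3% v 84.0% | 81.3% v 84.6% |
| 20% | .028 / .007 | 82.7% v 87.9% | 82.7% v 89.0% |

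The loss is 1.4 to 1.7 points at 5% and 2.7 to 3.3 points at 10%. The test becomes conservative, so false positives do not increase.

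**Which covariates are safe.** The random code is issued before consent is signed, and the questionnaire follows. It is on paper in the control arm, inside the game in the game arm, and web-based in the direct arm. Answers on number of partners and on intention to notify therefore come after allocation, by a mode that differs by arm. Number of partners is also tied to the denominator of the main outcome, the percentage of partners informed.

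**The case against.** **Silence is not exclusion.** A reader might infer that centre and known predictors are kept out of the model. The documents do not support that: no covariate is named, so none is excluded, and a condensed article may leave the list to an analysis plan that is not shown. This stands, and a missing list alone would be no finding. A later list would not by itself correct the stated baseline tests, the two-group test for three arms, or the stated basis for adjustment.

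**No stated selection rule.** A reader might infer that the baseline tests select the covariates. That link is suggested only by two adjacent sentences. It is a risk the wording leaves open, not a stated plan.

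**Differences may not be pure chance.** The arm is known before consent is signed, withdrawal is expected at 10% in the intervention arms against 20% in control, and infected partners enter in their index case's arm without their own randomisation. Some systematic imbalance is therefore possible. This stands as well, but a p-value is a poor guide to such imbalance, and the argument for fixed covariates becomes stronger.

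**Size.** A reader might turn an R² of 5% to 20% into 21 to 83 of the 416 index cases (0.05 × 416 and 0.20 × 416). That conversion does not hold: no R² is given in the documents, the arithmetic belongs to a linear model and does not carry over directly to a relative risk, and it assumes that the planned adjustment captures none of this variance. Nor is the 40% the chance that the primary result changes.

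**Stratified allocation is not spelled out.** The text describes a sample stratified by centre, and the targets by arm in Table 1 suggest that allocation is too, but no sentence says that the random list is stratified. If it is not, the conservative-size result falls away. The precision argument for including centre remains.

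**Conclusion.** The point holds in limited form. The article states baseline significance tests between randomised arms, names a two-group test for three arms, and rests the primary model on confounding variables. This invites adjustment driven by chance imbalance and leaves the design's stratification by centre without a stated place in the analysis. It does not establish data-driven selection, exclusion of centre, or an inflated type I error.

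The size is modest. There is about a 40% chance of at least one spurious baseline difference (10 independent tests at .05), and about 1 to 3 points of power are lost if centre is omitted and explains 5% to 10% of the variance. The variance share, the 80% reference power and the balance of arms within centre are all assumptions. Dropping the baseline tests alone changes no primary estimate. The gain comes from fixing the model.

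**What to change.** - Report baseline characteristics by arm with descriptive statistics, and remove the chi-square and t tests.
- Replace the phrase on confounding variables with a primary model fixed before outcome data are seen: arm, centre (7 levels), diagnosed STI as registered by the health professional, sex and age.
- Give a model with arm and centre only as a sensitivity analysis.
- Use number of partners as a covariate only if it is recorded before allocation in the same way in all arms.
- Do not adjust for intention to notify, which may already reflect the arm.

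Sex and date of birth sit on the same post-allocation questionnaire. The arm cannot alter them, but they could be missing for patients who never log in, so it would help if the professional recorded them at enrolment.

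The cost is mainly wording, since these variables are already collected. The downside is slight: a few more model terms, and possibly small cells in the smallest centres (Cerdanyola is planned at 12, 11 and 11 per arm).

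### The three-arm comparison is planned at a Bonferroni level of .016, but the analysis section sets .05 with 95% intervals, and nothing reconciles the two

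*Protocol article*

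**What the plan says.** The Design section states "This is an unblinded 3-armed randomized controlled trial". Its primary hypothesis is that more partners are informed "in the intervention groups compared with the control group".

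The Sample Size section says the participants were distributed over the three arms "according to the Bonferroni correction, to allow multiple comparisons of outcomes with a significance level of *P*=.016". It aims "to have at least 120 participants in each 1 of the groups" and inflates that number for withdrawals to 133, 133 and 150.

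The Data Analysis section says that regression with adjustment "will be used to evaluate the primary outcome and relative risk, and its 95% CIs will be calculated". The next sentence is "Significance will be set at .05". The section names no Bonferroni level, global test, testing order or other control of multiplicity, and it does not refer back to .016.

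**The concern.** The article gives two significance levels for comparing the same arms. This is a conflict between two statements, not a detail left to a fuller document: a separate analysis plan would have to override one of them or explain how they fit together.

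The stake is any primary comparison with P between .016 and .05. It counts as a success under Data Analysis and a failure under Sample Size. If the matter stays open, the choice can be made once the results are known. The Conclusions section says that the app may be rolled out across Catalonia if shown effective, so the rule for that claim should be fixed beforehand. The Results section describes recruitment as still under way, so at that stage the rule could still be settled prospectively.

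**Working it through.** **Inputs.** Per-comparison level .016, 120 evaluable per arm, and 133, 133 and 150 recruited (Sample Size). Level .05 and 95% intervals (Data Analysis). Three arms, with the primary hypothesis set against control (Design).

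**1. The plan's own figures.**
- Withdrawals: 120/0.90 = 133.3 and 120/0.80 = 150. The total is 133 + 133 + 150 = 416, as stated.
- Bonferroni: .05/3 = .01667, which gives .016 by truncation. Two comparisons would give .05/2 = .025, which does not match. The level .016 therefore implies three pairwise comparisons.
- The 120 per arm cannot be reproduced, because no power, effect size or control-arm rate is given.

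**2. Family-wise error if .05 is applied to each comparison.** The assumptions are no true difference between any arms, approximately normal estimates and equal variance. Pairwise tests share arms and so are correlated.
- *Three pairwise tests, equal arms.* The error is the chance that the studentized range of three means exceeds 1.960 × √2 = 2.772, which is 12.2%. Simulation gives 12.2% with arms of 120/120/120 and also with 150/133/133. For comparison, independent tests would give 1 − 0.95³ = 14.3%.
- *Two comparisons with control only.* The error is 9.1% with equal arms (correlation 0.5) and 9.2% with 150 controls and 133 in each intervention arm (correlation 133/283 = 0.47). Independent tests would give 1 − 0.95² = 9.75%.
- *Joint coverage of three 95% intervals.* 100% − 12.2% = about 88%.

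**3. Family-wise error if the Bonferroni level is applied.**
- Three tests at .016: 4.2% (upper bound 3 × .016 = 4.8%).
- Three tests at .05/3: 4.4%.

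**4. Matching intervals.** A test at .016 corresponds to a 98.4% interval, and a test at .05/3 to a 98.3% interval. At .05/3 the multiplier is 2.394 instead of 1.960, and 2.394/1.960 = 1.22, so the interval is about 22% wider (about 23% at .016, where the multiplier is 2.409).

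**5. The alternative of a global test first.** Take a 2-degree-of-freedom test at .05, followed by pairwise tests at .05 only if it is significant. With exactly three arms this controls the family-wise error at 5%. Its power was simulated for a pairwise contrast that has 80% power at an unadjusted .05, with equal arms:

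| Rule | Power |
|---|---|
| Unadjusted .05 | 80% |
| Global test first, third arm equal to one of the two compared | 76% |
| Global test first, third arm midway between them | 70% |
| Bonferroni, .05/3 | 66% |

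**The case against.** The strongest reply is that the two levels can coexist: .05 is the overall level and .016 is each comparison's share of it. The Sample Size section says the lower level exists to allow multiple comparisons. The .05 sentence is generic, and its paragraph also covers baseline chi-square and t tests. On that reading no test is inflated. This stands as a possible reading, so a reader who infers that the trial's family-wise error simply is 12% goes further than the text allows. But the article does not state that reading. The .05 sentence directly follows the primary analysis without restriction, and the 95% intervals do not fit it. A relative risk whose 95% interval excludes 1 could still fail at .016, and the article does not say which result governs.

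A second reply is that 12% uses the largest family, while the primary hypothesis concerns intervention against control. That is fair: for those two comparisons the figure is about 9%. If the two interventions were pooled against control there would be a single test and no inflation. But .016 itself implies three comparisons, and both unadjusted families exceed 5%.

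A reader might also infer that the sample size depends on .016. The section names that level, but without a power or effect size the 120 per arm cannot be traced to any level. The section also cites about 400 young people a year at the centers, which would fit a number chosen for feasibility.

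**Conclusion.** The conflict is real and should be resolved before the data are analyzed. Its size depends on how Data Analysis is read:

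- .05 applied to each of three pairwise comparisons: family-wise error about 12%.
- .05 applied to each of the two comparisons with control: about 9%.
- .05 as the overall level with .016 per comparison: about 4%, but with intervals that do not match the tests.

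These figures assume no true differences between arms and approximately normal estimates of equal variance. They barely change between 120 per arm and the recruited numbers. The documents do not establish that the correction has been abandoned, only that the section governing the analysis omits it and gives a different level. No change to the design, data collection or sample size follows from this point.

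**What to change.** In Data Analysis, replace the significance sentence with wording to this effect: the family-wise level for the primary outcome is .05; each of the three pairwise comparisons is tested at the Bonferroni level given under Sample Size (.016, that is .05/3), with confidence intervals of the matching level (98.4% for .016, 98.3% for .05/3); a level of .05 with 95% intervals applies only to secondary and descriptive analyses. One of .016 and .05/3 should be used in both sections.

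The cost is one sentence, and primary intervals about 22% wider than 95% intervals.

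A global test at .05 followed by pairwise tests at .05 is a valid alternative with more power than Bonferroni. It is not free: power falls to about 70 to 76% where an unadjusted pairwise test has 80%. It also leaves the joint coverage of three 95% intervals at about 88%, so the intervals would still need their own adjustment or a clear label as unadjusted.

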### Confidentiality, Storage, and Archiving

Data will be archived in a safe environment, according to the European Data protection law.

### Ethical Aspects

The investigators are committed to respect the prevailing norms of Good Clinical Practice, the requisites of the Declaration of Helsinki, and the clauses of general and particular ethical conditions related to the right to privacy, anonymity, and confidentiality. Neither the first name nor surname or any other type of data indicating the identification of the young population will be registered. Therefore, identification will be made by alphanumeric codes. Youngsters participating in the study will sign an Informed Consent by paper, and when they are enrolled through the Web, they will confirm acceptance to participate by clicking on the confirmatory cell.

## Results

The Web app was available to the health professional to initiate recruitment by early April 2018. From April 1 to May 30, we expected to recruit 83 index cases, but difficulties on accreditation of new health professionals and on entry to the study environment in the Web prevented recruitment. In early June 2018, there were 32 young people who accepted to participate in the study. They were assigned randomly to control group (n=15), game intervention group (n=9), and Web direct intervention group (n=8).

The project is currently recruiting with a rate of approximately 6 recruitments per month. Recruitment is slower than expected. Mainly because of the difficulties in the implementation of the Web app. Our confidence is that within the last 6 months of the field study, recruitment pace will be doubled, and the expected sample size will be achieved. To improve recruitment, since September 2018, we have allocated 3 more professionals to the task.

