### Study Period

The study will be conducted within a 3-year period. A total of 1 year to prepare the Web app, 18 months for the field work, and 6 months for the evaluation and dissemination of results.

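### Doubling a pace of about 6 recruits per month in the last 6 months projects to about 164 index cases, not the 416 that the article says will be achieved

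*Protocol article*

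**What the plan says.** All figures are in the protocol article.

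- **Target.** The Design section states: "We will randomize 416 young and recently diagnosed index cases in 1 of the 7 centers of the study". The Sample Size section derives this from 120 completers per arm: "to have at least 120 participants in each 1 of the groups, 133 are recruited in each 1 of the intervention groups and 150 are" planned for control. It assumes "10% of withdrawals after recruitment within the intervention groups and 20% of withdrawals after recruitment within the control group".
- **Time.** The Study Period section allows "18 months for the field work". The Sample Size section allows recruitment to run for 13 to 18 months.
- **Source population.** The Sample Size section says: "Young population accessing all centers of study within a year is around 400".
- **Progress.** The Results section says that the Web app opened for recruitment in early April 2018, that 83 index cases were expected by 30 May, and that 32 young people had accepted by early June. It continues: "The project is currently recruiting with a rate of approximately 6 recruitments per month". It calls this slower than expected and reports that three professionals were added from September 2018. It then states the authors' confidence that "within the last 6 months of the field study, recruitment pace will be doubled, and the expected sample size will be achieved".

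**The concern.** The Results section gives a rate, a multiplier, the period to which the multiplier applies and the result that should follow. These can be checked against each other, and they do not agree: 12 per month for 6 months adds only 72 recruits, while the gap to 416 is several hundred.

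The planned precision is at stake. The trial is sized for at least 120 per arm, with pairwise comparisons at P=.016. If accrual followed the stated rates, each comparison would rest on well under half that number, and a null result would say little about effects of moderate size. A reader of the article would still believe that the full size was in reach.

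**Working it through.** **1. Reproduce the target.** With n/(1 − d): 120/0.9 = 133.3 (stated as 133) and 120/0.8 = 150. Then 133 + 133 + 150 = 416. The target follows from its inputs.

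**2. Project accrual on the stated rates.** Assume that the 18 months start in April 2018, that early June is the end of month 2, and that doubling means twice the current 6 per month.

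| Period | Rate | Recruits |
|---|---|---|
| Months 1–2 | count given | 32 |
| Months 3–12 | 6 per month | 10 × 6 = 60 |
| Months 13–18 | 12 per month | 6 × 12 = 72 |
| Total | | 164 |

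164/416 = 39.4%. With the 13-month window the total is 32 + 5 × 6 + 6 × 12 = 134 (32%).

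**3. Pace needed.** At month 12 the count would be 32 + 60 = 92. The gap is 416 − 92 = 324, and 324/6 = 54 per month, which is 54/6 = 9 times the current pace. The stated source population gives 400/12 = 33.3 per month.

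**4. More favourable readings.**

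- Pace doubled for all 16 months after early June: 32 + 16 × 12 = 224 (54%).
- Early average of 32/2 = 16 per month for 12 months, then 32 per month: 192 + 192 = 384 (92%).
- Doubling taken to mean twice the average planned pace, 416/18 = 23.1 per month: 92 + 6 × 46.2 = 369 (89%).
- Twice the pace needed for a 13-month window (416/13 = 32), or twice the pace expected in the first two months (83/2 = 41.5), would pass 416. That means 64 or 83 per month, about two to two and a half times the 33 per month above.
- 6 per month taken as a figure per centre: 7 × 6 = 42 per month. The article gives the rate for the project, and 42 per month would match the expected 41.5, so recruitment would not be slower than expected.

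For doubling in the last 6 months to reach 416, the base pace r must satisfy 32 + 10r + 12r = 416. This gives r = 384/22 = 17.5 per month, nearly three times the stated 6.

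**5. Analysable per arm at 164.** Using the planned split of 150:133:133:

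- Control: 164 × 150/416 = 59.1, and 59.1 × 0.8 = 47.
- Each intervention arm: 164 × 133/416 = 52.4, and 52.4 × 0.9 = 47.

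**6. Illustrative precision.** The Sample Size section as printed gives neither a power nor a control rate. Assume 80% power, two-sided .016, a control rate of 30% to 50%, and one binary outcome per index case. The detectable difference d solves

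d = z(0.992) √(2 p̄(1 − p̄)/n) + z(0.80) √([p₁(1 − p₁) + p₂(1 − p₂)]/n),

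with p₂ = p₁ + d, p̄ the mean of p₁ and p₂, z(0.992) = 2.409 and z(0.80) = 0.842.

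| Per arm | p₁ = 30% | p₁ = 40% | p₁ = 50% |
|---|---|---|---|
| 120 | 20.5 points | 20.9 points | 20.4 points |
| 47 | 33.0 points | 32.8 points | 31.4 points |

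**The case against.** The strongest defence is that this is a status remark, worded as confidence and placed beside an open admission of slow recruitment. No randomisation, outcome or analysis rule depends on it. The pace is approximate and is attributed mainly to Web app difficulties, and staff were added. All of this is fair, and it limits how far the point reaches. It does not rescue the sentence: the only effect claimed for the improvements is the doubling, and the projection already includes it.

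The source-population ceiling is softer than it looks. The figure of 400 is approximate. Infected partners who arrive without a code are enrolled as new index cases. The plan itself expected 41.5 per month at the start, above 33. The ceiling therefore supports the argument but does not carry it; the ninefold gap does.

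The size of the shortfall also depends on which rate is used. The article implies 16 per month up to early June and 6 per month at the time of writing, and does not reconcile them. On the higher rate the shortfall is 8%, on the lower 61%.

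Three stronger readings are tempting and are not supported:

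- A reader might apply 6 per month from the first month and get 12 × 6 + 6 × 12 = 144. That credits 12 recruits by early June where the article reports 32, so it drops 20 documented recruits.
- A reader might infer that the trial will certainly miss 416. The documents show only that the stated rates do not lead there.
- A reader might conclude that the primary contrast should become both Web arms pooled against the paper card, at .05. That would change the primary comparison of an unblinded trial after randomisation had begun. It is a debatable trade-off, longer recruitment is an alternative, and an arithmetic error in a progress statement does not settle it.

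**Conclusion.** The point holds as a contradiction between a stated result and the figures beside it. On the article's count of 32 and its current pace, doubling in the last 6 months projects to about 164 index cases, or about 47 analysable per arm against 120. None of the readings checked reaches 416 without a monthly pace above the stated source population or a conflict with the article's own account of slow recruitment.

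The figure of 164 assumes 18 full months from April 2018, 6 per month from early June to month 12, and 12 per month after that. The article gives no count after early June, so the true position at the time of writing may differ.

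The rise in the detectable difference from about 20–21 to about 31–33 points is an illustration. It rests on an assumed power and control rate and on one binary outcome per index case. The main outcome is the percentage of partners informed, and an index case may have several partners, so the actual precision could differ.

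**What to change.** In the Results section, replace the statement that the expected size will be achieved with a projection conditional on stated rates: the count to date, the pace used for each period and the resulting total (about 164 on the present figures). Explain how 32 recruits in about 2 months fits with a current pace of 6 per month, because this choice moves the projection more than any other. Then restate the expected number per arm after withdrawals (about 47 on the present figures) and the detectable difference or confidence-interval width that goes with it, naming the assumed control rate, the power and the unit of analysis.

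The cost is a few sentences and a less favourable stated size. No design or analysis rule changes. Whether to recruit for longer or to pre-specify a different primary contrast is for the sponsor to decide and document before outcome data are seen; it is not part of this correction.
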